#### Data cleaning and missing data

All data will be reviewed for valid values/data entry errors, outliers, and extent/pattern of missing data. Descriptive statistics will be reviewed. Consistency and logic checks will be applied for review/cleaning. The multiple group analysis models will provide valid estimates of efficacy if the proportion of missing values is < 10%. Analysis will be conducted at the patient/family, provider, and institution levels. The effect of program size and cohort will be examined and controlled if needed.
H2.1. ANOVA will compare the effectiveness of the two implementation strategies on penetration and health equity. The outcomes are proportions: families screened/families eligible, families provided feedback/families screened, ethnic minority families screened/ethnic minority families eligible, low SES families screened/low SES families eligible. ICCs among the clusters will be calculated and used to adjust for the cluster effect [67, 68].H2.2. Three sets of outcome variables—perception of implementation, engagement in addressing health disparities, and burnout/job satisfaction—will be tested. A two group analysis using Structural Equation Modeling (SEM) will compare the effectiveness of the two strategies [69, 70]. To test the effect of time, we will conduct latent growth curve analysis [71–73]. Analyses will be conducted using Mplus 5.0 [74] with ML estimation for outcome variables that meet the distribution assumptions, and WLSMV estimation for variables that do not. Potential mediating effects of favorable perception of implementation on provider job satisfaction and burnout will be examined using mediation models. TIER is expected to be associated with more favorable perceptions of implementation, less burnout, and higher job satisfaction.H2.3. At the institution level, adoption of the PAT will be measured by a ratio of sites that initiate implementation/sites that agreed (H2.3a). If substitutions are necessary, sites that are newly invited will be added to the denominator and adoption calculated by total acceptances/total invited. ANOVA will be conducted to compare the effectiveness of the two strategies. For H2.3b sustainability (PIQ perceptions of implementation benefits and challenges), ANOVA will be conducted to compare the effectiveness of the two strategies on benefits and challenges. For H2.3c, we are interested in the extent to which psychosocial care is matched to need. A cost-effectiveness threshold or criterion to which to compare costs of screening with these two implementation strategies has not been established, necessitating our consideration of valued outcomes in the psychosocial screening literature and resources available. We will use a data analytic approach that we used previously [18]. ANOVA will be conducted to test whether psychosocial care is matched with levels of psychosocial risks, resulting in a 2 (strategy) × 3 (psychosocial risks: clinical, targeted, universal) design on equitable distribution of services and costs of care. It is expected that the 3 PPPHM levels will be related to number and costs of services provided as measured on the PSMTC, with least at universal and most at clinical. It is expected that TIER will result in a better match between level of risk and services provided. Scores from the PSMTC will be derived and mapped onto the levels of the PPPHM. Additional analyses will be conducted to compare English speaking and Spanish speaking families, different ethnicity, race, and SES and insurance status on the outcome variables for H2.3c.

#### Aim 3

We will summarize the data by item and then aggregate the results across participants to reflect potential problems with Toolkit components and to identify components that are clear and supportive of effective implementation [56]. To ensure rigor, we will systematically analyze and then summarize the interview data following a formal coding scheme. Subsequently, we will develop a cognitive interviewing outcome report, a description of the number and type of participants and interviews completed, a description of the specific procedures used in the interviews and the interview guide, and a written summary of feedback on each of the components [56]. This report will be distributed to the study team who will discuss the issues identified. Decisions will be documented in a tracking matrix [75]. Based on this feedback, with aim 2 data and theoretical frameworks, we will revise and finalize the Toolkit.

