### Cluster-randomized comparative effectiveness trial (aim 2)

PAT implementation will be tested using a head-to-head randomized implementation (comparative effectiveness of two implementation strategies) trial initiated in three cohorts of 1 year each (2021, 2022, 2023). All 18 pediatric cancer programs invited to participate in the trial agreed to a 2-step randomization process stratified by size of site; sites will be randomized to one of three cohorts and then to strategy, comparing strategy I (training) with strategy II (TIER).

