#### Selection of sites

The following criteria were used in site selection:
*Provide staff and tablet computer for screening*. Each site agreed to provide the staff person(s) screening and tablets. Each site will be provided support for a portion of the site PI’s effort and a part-time research coordinator based on center size for purposes of research only (the research coordinator will not do the screening).*Center size*. Because program size is related to the size of the psychosocial team and related psychosocial resources [5], we used PIPS-CSS data to stratify by size to obtain three equal and clinically relevant groups based on number of new pediatric cancer patients annually—small (30–60), medium (61–149), and large (150+). We selected 6 sites for each of the three size categories.*Psychosocial staff*. To assure that there are staff to conduct screening and act on the results of screening, selected sites are at or above the median for the size of their psychosocial team (number [full time equivalents] social workers + psychologists + psychiatrists + child life specialists) [5] based on PIPS-CSS data.*Diversity of population*. We selected centers in states with a high percentage of ethnic or racial minority families and/or families with socioeconomic disadvantage. CA, TX, FL, NY, and NJ have large Hispanic populations [42]. AL, NC, and VA have the most rapidly increasing Hispanic populations, and AL, LA, NC, and VA have the largest percentage of African-Americans [43]. Thirteen out of 18 sites are in these states. Twelve out of 18 are in states with > 20% of children living in poverty [44]. Other sites were selected to balance geography, race, ethnicity, and SES.

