PAT implementation will be tested using a head-to-head randomized implementation (comparative effectiveness of two implementation strategies) trial in three cohorts over 3 years. *Randomization*. Eighteen sites will be randomized to one of three cohorts. Each cohort will be further randomized to one of the two strategy conditions. Randomization will stratify sites by size to maximize internal validity and statistical power. Sites will be randomized by a data analyst not connected with the study using a two-step Excel = RAND() function. The sequence will be stored in a password-protected electronic file. *Sample size*. The estimated sample of patients/families is based on the median number of new patients each year from the PIPS-CSS database: small (*n* = 60), medium (*n* = 92), large (*n* = 339) multiplied by 6 sites at each size, a total of 2946, with 1473 families allocated to each strategy. With an anticipated Interclass Correlation Coefficient (ICC) [65] of .005, the effective sample size is 950 per arm, a sample size that is sufficient to detect a small effect between the two strategies given 80% power (alpha = .05, one sided). We project a Hispanic sample of 20% of the total (*n* = 589). Based on our research [8], approximately 30% of Hispanic caregivers will be more acculturated/not literate in Spanish at the level necessary to complete the Spanish PAT, rendering a sample of 412. With an anticipated ICC of .005, the effective sample size is 224 which is sufficient to detect a medium effective between the English and Spanish versions given 80% power (alpha = .05, one sided). At the provider level, each of 18 sites has a PI and up to four people screening, and for TIER sites, a champion. Therefore the staff sample ranges from a minimum of 45 ([18 × 2] + 9) to a maximum of 99 ([18 × 5] + 9), likely in the middle given the range of size of sites. At the institution level, 18 sites will be randomly assigned to one of two strategies (9 sites/group). These sample sizes are comparable to other implementation science studies [66].

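### Size and cohort, the factors used to randomise sites, are controlled only under an undefined, data-dependent condition; both should be fixed terms in the main strategy comparisons

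*Protocol article*

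**What the plan says.** The protocol article describes a two-step allocation in the section on the cluster-randomized trial (aim 2): sites go first to one of three yearly cohorts (2021, 2022, 2023) and then to a strategy, stratified by size. Data analysis, Aim 2, gives the reason for stratifying: "Randomization will stratify sites by size to maximize internal validity and statistical power". It also makes cohort a block for the strategy allocation: "Each cohort will be further randomized to one of the two strategy conditions". Under Selection of sites, "We selected 6 sites for each of the three size categories", and size is expected to matter: "Because program size is related to the size of the psychosocial team and related psychosocial resources". There are to be 9 sites per strategy.

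Under Data cleaning and missing data, the only statement on how these factors enter the analysis is "The effect of program size and cohort will be examined and controlled if needed". The hypothesis paragraphs that follow do not add to it. For H2.1, "ANOVA will compare the effectiveness of the two implementation strategies on penetration and health equity". H2.2 uses a two-group structural equation model, H2.3a and H2.3b use ANOVA, and H2.3c uses a strategy by risk-level ANOVA. None of these names size or cohort as a term.

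**The concern.** Whether a randomisation factor belongs in the model follows from the allocation and not from the outcome data. Balancing strategy over size and cohort makes the estimated difference less variable, but the test benefits only if the analysis also removes the size and cohort variance from the error term. If it does not, the standard error is too large and the test is conservative.

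A rule of looking first and then deciding raises two separate problems:

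- **Precision.** Eighteen sites give little power to show that control is needed, so useful adjustment may be dropped by chance.
- **Choice of model.** With no criterion stated, the decision can be made separately for each outcome after both versions of the result are known.

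The stated purpose of stratification and the stated analysis rule therefore do not fit together. With 9 sites per arm, little precision can be spared.

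**Working it through.** The plan states no figure for the gain from stratification. Its sample-size paragraph works in families and does not use size or cohort, so there is nothing to reproduce and the check is a fresh calculation.

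**Inputs from the protocol article.** 18 sites, 6 per size, three cohorts, 9 per strategy, one-sided .05.

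**Assumptions, not in the documents.**

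- Equal cohorts, with one site per strategy in each of the 9 size-by-cohort cells.
- Analysis of site-level means, with total between-site variance 1 apart from the strategy effect.
- A share R² of that variance due to size (two thirds of it) and cohort (one third), varied from 0 to 0.5.
- A true strategy difference of 1.0 site-SD.
- Need read as a joint F-test of size and cohort at .05.

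**Always adjusting (18 − 6 = 12 df).** The standard error is √[(1 − R²)(1/9 + 1/9)], so the non-centrality of t is 1.0/√[0.2222(1 − R²)]. This is 2.12, 2.37, 2.54 and 3.00 at R² = 0, 0.2, 0.3 and 0.5. From the non-central t, power is 64%, 72%, 77% and 88%.

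**Never adjusting (16 df).** The expected error mean square is [16(1 − R²) + 18R²]/16. At R² = 0.3 this is (11.2 + 5.4)/16 = 1.04, while the difference between arms really varies according to a variance of 0.70. The test is therefore conservative.

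**How often control is found to be needed.** The F-test on 4 and 12 df has non-centrality 18R²/(1 − R²). This is 4.5, 7.7 and 18 at R² = 0.2, 0.3 and 0.5, so the test is significant in 25%, 42% and 81% of trials.

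**Results.** Power for never adjusting and for the F-test rule, and all error rates, come from 200,000 simulated trials per cell.

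| R² | Need found | Power: never | Power: F-test rule | Power: always | Type I: never | Type I: F-test rule | Type I: always |
|---|---|---|---|---|---|---|---|
| 0 | 5% | 65% | 66% | 64% | .049 | .052 | .050 |
| 0.2 | 25% | 66% | 70% | 72% | .032 | .044 | .049 |
| 0.3 | 42% | 66% | 74% | 77% | .024 | .045 | .050 |
| 0.5 | 81% | 67% | 86% | 88% | .009 | .048 | .050 |

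**Free choice of model.** If the smaller of the adjusted and unadjusted p-values is taken, the one-sided error rate at R² = 0 is about .055.

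**The case against.** A reader might infer that the plan throws away its stratification, at a cost of 66% v 77% power, or even 67% v 88%. The documents do not support that. Those contrasts set never adjusting against always adjusting, and the plan allows for adjustment. Under the F-test reading the loss is 2 to 3 points. With a looser criterion of p < .20 it vanishes: about 77% v 77% at R² = 0.3 and 88% v 88% at 0.5. The error rate also stays near nominal under the F-test rule, and never adjusting errs on the safe side. All of this stands, and it sets the size of the point.

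Other limits also stand:

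- The article names no test, so the F-test reading is itself an assumption.
- The power purpose is stated for size only. Cohort belongs in the model because strategy is randomised within it.
- The figures 60, 92 and 339 are median annual new patients by size category. They are not the range of site sizes and do not show how strongly size affects the outcomes.
- Adjustment cannot sensibly be required everywhere. Adoption (H2.3a) is a ratio of sites initiating to sites agreeing, and all 18 invited sites have agreed. With few or no non-initiators, four extra terms may not be estimable. H2.2 involves latent-variable models on 45 to 99 staff.

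It can also be said that an article may leave the meaning of need to a fuller plan. That carries less weight, because the article does not stay silent. It states a conditional rule, and a later plan that always adjusted would have to depart from it.

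**Conclusion.** The point holds as a modest but real flaw. Control of the randomisation factors rests on an undefined decision taken after seeing data, which does not fit the article's own reason for stratifying. Under an F-test reading, the expected loss against always adjusting is about 2 to 3 power points when size and cohort explain 20% to 50% of between-site variance. It would be larger (about 11 points at 30% and 21 at 50%) only if the factors were in the end left out. If they explain nothing, always adjusting costs about 1 to 2 points.

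The freedom to choose a model for each outcome does not depend on the variance share. Its numerical effect is small (error about .055 at worst in this model), but it leaves the main comparison open to challenge for no benefit. The sizes rest on the assumed variance shares, the 1.0 site-SD effect, the balanced cells and the site-level analysis.

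**What to change.** Replace the sentence under Data cleaning and missing data with a commitment along these lines: size stratum and cohort are included as fixed terms in the strategy comparisons for H2.1, H2.3b and H2.3c, and as covariates in the H2.2 models where estimable, whatever their observed effect. The unadjusted model is reported as a sensitivity analysis. The H2.3a adoption ratio may stay unadjusted.

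This needs no new data. In site-level models it uses 4 of the 16 residual degrees of freedom (two for size, two for cohort), at the cost of 1 to 2 power points given above if neither factor matters. The H2.2 models need their own check that the added covariates can be estimated with the staff numbers available.

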**Fig. 2 Fig2:**
[figure not shown]
Interactive systems framework and stages of the implementation study

#### Aim 1

Refine strategies I (training) and II (TIER) using semi-structured interviews with stakeholders—parent advocates, multidisciplinary health care providers, national pediatric oncology professional organizations, and health care industry leaders (implementation team).

#### Aim 2

Compare the two theoretically based and empirically informed strategies to implement the PAT in English and Spanish using a cluster-randomized controlled trial. Compared to training:

**H2.1**. At the patient/family level, TIER will be associated with: (a) a higher proportion of families of newly diagnosed children screened and provided with feedback (penetration) and (b) higher rates of screening for ethnic minority and socioeconomically diverse families (health equity).

**H2.2**. At the provider level, TIER will be (a) more feasible and rated as appropriate and acceptable, (b) associated with greater engagement in addressing health disparities, and (c) associated with less burnout and better job satisfaction.

**H2.3**. At the institution level, TIER will be associated with: (a) a higher rate of site participation (adoption), (b) more positive perceptions of implementation benefits and fewer challenges (sustainability), and (c) psychosocial care better matched to need demonstrating a more equitable distribution of services and costs of care.

#### Aim 3

Based on the results of the trial and further guidance from the implementation team, we will integrate acceptable, feasible, and effective strategies to develop and disseminate a web-based PAT Implementation Toolkit.

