#### Measurement/outcomes (all sites)

The measures assess outcomes across patient/family, provider, and institution levels (Table 1) that are clearly operationalized and reproducible [46]. Site PIs and coordinators will attend training on data collection procedures, in separate sessions for the two conditions.

**Table 1 Tab1:** Measurement

Level/Hyp	Concept	Source	Metric/measure
Patient/family 2.1	Penetration Health equity	EHR (monthly)	Demographics: race, ethnicity, zip code, insurance No. eligible families, English/Spanish No. eligible families screened, English/Spanish % Family feedback letter provided
Provider 2.2	Feasibility Appropriateness Acceptability Engagement in addressing health disparities Job satisfaction Burnout	Survey (Pre, 6-month, Post)	Acceptability of intervention measure Intervention appropriateness measure Feasibility of intervention measure AREA scale of physician engagement Satisfaction employees healthcare Maslach Burnout Inventory version for Medical Personnel
Institution 2.3	Adoption Sustainability: perceived benefit Cost-effectiveness: services/need and cost	Survey	Site participation rate PAT implementation questionnaire
		EHR (monthly)	Psychosocial Services and Medical Treatment Checklist Intensity of Treatment Rating Scale

At the patient/family level (Hyp 2.1) the site coordinator will extract EHR data and send the coded data via REDCap to the data core. The following data for English and Spanish versions of the PAT will be reported monthly: new patients meeting eligibility requirements per the PAT implementation plan; patients with documentation of PAT screening; patients receiving feedback letter; demographic data on all eligible and all screened (race, ethnicity, zip code, insurance).

At the provider level (Hyp 2.2), the site PI and screeners will complete the following self-report measures (~ 15 min) at baseline (T1), and 6 (T2) and 12 (T3) months via REDCap: acceptability of intervention measure; intervention appropriateness measure and feasibility of intervention measure [47]; measure of physician engagement in addressing racial and ethnic health care disparities [48], satisfaction of employees in healthcare survey [49], and Maslach Burnout Inventory [50].

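### The feedback half of H2.1a is compared only among screened families, although the hypothesis concerns all newly diagnosed families

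*Protocol article*

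**What the plan says.** In the protocol article, Specific aims, Aim 2, H2.1(a) predicts that TIER will be associated with "a higher proportion of families of newly diagnosed children screened and provided with feedback (penetration"). The population is newly diagnosed families, and the event is being screened and receiving feedback.

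The analysis paragraph for H2.1 (Data analysis, Aim 2, under Data cleaning and missing data) states that "ANOVA will compare the effectiveness of the two implementation strategies on penetration and health equity". It then defines the outcomes. The first is given as "The outcomes are proportions: families screened/families eligible". The second is "families provided feedback/families screened". The remaining two are screening proportions in ethnic minority and low-SES families, each over the eligible families of that group. Feedback is the only one of the four whose denominator is not eligible families, and no outcome divides feedback by eligible families.

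Table 1 (Measurement/outcomes, all sites) lists a percentage for "Family feedback letter provided" without a denominator, so it does not settle the matter. The text below the table says that sites report each month: "new patients meeting eligibility requirements per the PAT implementation plan; patients with documentation of PAT screening; patients receiving feedback letter".

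**The concern.** Randomisation assigns sites, and with them all their newly diagnosed families, to a strategy. Being screened comes later, and H2.1 itself predicts that it will differ between strategies. Restricting the feedback comparison to screened families therefore compares two groups formed by the strategies and not by randomisation. A difference in feedback/screened may reflect which families were screened as much as how well feedback was delivered.

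Three consequences follow.

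- The ratio does not measure the proportion that H2.1a names. A family that is never screened, and so never receives feedback, does not count against the strategy.
- It can point the other way from the named proportion when one strategy screens more families but gives feedback to a somewhat smaller share of them.
- A site that screens nobody has a ratio of 0/0 and disappears from the comparison, although its reach with feedback is zero. This is not far-fetched: the Background reports that 9 of 12 centers in the pilot implemented the web-based PAT, and H2.3(a) expects adoption to differ by strategy. With 9 sites per arm, even one such loss matters.

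The paragraph also gives no rule for reading H2.1a if its screening and feedback proportions disagree.

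**Working it through.** **Inputs from the protocol.** Median new patients per year are 60, 92 and 339 for small, medium and large sites, with 6 sites of each size (Data analysis, Aim 2, Sample size). The totals reproduce: 6 × (60 + 92 + 339) = 2946, and 2946 / 2 = 1473 per strategy, as stated ("a total of 2946, with 1473 families allocated to each strategy"). These count all new patients, not screened ones.

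The effective sample size ("of .005, the effective sample size is 950 per arm") is not used here. The usual equal-cluster formula, with 1473/9 = 163.7 families per site, gives 1473 / [1 + 162.7 × 0.005] = 1473 / 1.813 ≈ 812. That difference is a separate matter and does not bear on this point.

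**Inputs assumed.** The protocol gives no expected screening or feedback rates. All rates below are assumptions.

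**Formula.** Let s be screened/eligible and f be feedback/screened. Since feedback follows screening,

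feedback/eligible = s × f.

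Feedback/screened favours Training while feedback/eligible favours TIER whenever f(Training) > f(TIER) and s(TIER)/s(Training) > f(Training)/f(TIER).

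**Main illustration.** TIER: s = 0.80, f = 0.80. Training: s = 0.60, f = 0.85.

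- Feedback/screened: 80% v 85%, so TIER is 5 points behind.
- Feedback/eligible: 0.80 × 0.80 = 64% v 0.60 × 0.85 = 51%, so TIER is 13 points ahead.
- Condition for reversal: 0.80/0.60 = 1.33, which exceeds 0.85/0.80 = 1.06.
- With 1473 eligible families per arm, the denominators of the planned ratio are 0.80 × 1473 ≈ 1178 (TIER) and 0.60 × 1473 ≈ 884 (Training). Families given feedback number 0.64 × 1473 ≈ 943 v 0.51 × 1473 ≈ 751.

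**Range of assumed rates.**

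| Training s / f | TIER s / f | Feedback/screened, TIER v Training | Feedback/eligible, TIER v Training |
|---|---|---|---|
| 60% / 80% | 80% / 80% | 80% v 80% | 64% v 48% |
| 60% / 85% | 80% / 80% | 80% v 85% | 64% v 51% |
| 50% / 90% | 80% / 80% | 80% v 90% | 64% v 45% |
| 40% / 90% | 80% / 80% | 80% v 90% | 64% v 36% |
| 30% / 95% | 90% / 80% | 80% v 95% | 72% v 28.5% |

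The first row has no reversal: the planned ratio shows no difference while reach with feedback differs by 16 points. If TIER did at least as well as Training on both steps, the two measures would not point in opposite directions.

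**What the plan's other outcome shows.** In every row TIER leads on screened/eligible, by 20 to 60 points (80% v 60% up to 90% v 30%). The plan compares that proportion directly.

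**The case against.** The strongest reply is that the plan already covers the missing denominator. Screened/eligible is the first outcome listed. Screening and feedback are successive steps, so the two listed ratios multiply to the desired proportion, and all three counts are collected. Separate ratios also show at which step a strategy fails, which a single proportion hides. H2.1a can be read as two steps and not as one joint event. The article names no primary outcome, and a fuller analysis plan may exist.

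Much of this stands. A reader might infer that a strategy which screens few families could win H2.1a, or that the answer to H2.1a would be reversed. The document does not support that: such a strategy would lose on screened/eligible, and nothing lets the feedback ratio override it. The most that could occur is a split result. A reader might also suppose that low-screening sites pick the families easiest to reach and so score well on feedback. That is a plausible mechanism, but the protocol does not say it, and the point does not need it.

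Two things survive. The product can be computed within a site or from pooled counts, but the plan does not list it as an outcome, and separate comparisons of its two factors are not a comparison of the product. And on either reading of H2.1a, the feedback comparison stays conditioned on an event after randomisation. The outcome is stated expressly, so this is not a detail that the article merely left to another document.

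**Conclusion.** The point holds for the feedback component of H2.1a. The hypothesis refers to newly diagnosed families, the feedback outcome refers to screened families, and the strategies are expected to change who is screened. The component can be reversed under unremarkable rates: 5 points in favour of Training on the planned ratio against 13 points in favour of TIER on the named proportion. These rates are assumed, and a reversal requires TIER to do worse than Training on feedback among the screened, which the protocol neither predicts nor excludes. Without a reversal, the planned ratio can still miss a real difference in reach.

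The screening component is correctly defined, and H2.1a as a whole is not reversed. I take the plan's count of eligible families, set by each site's implementation plan, as its working count of newly diagnosed families, as the screening outcome already does. Severity is moderate.

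**What to change.** In the H2.1 analysis paragraph, replace the feedback outcome by families screened and provided feedback over families eligible, and compare it between strategies alongside screened/eligible. Count a site that screens nobody as zero on both. Keep feedback/screened, but label it a descriptive process measure that is not a randomised comparison. State the same denominator for the feedback percentage in Table 1.

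The cost is a line or two of text. Eligible, screened and feedback-letter counts are already reported monthly, so no new data are needed, and the change should be made before the strategies are compared.

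### The H2.1(b) health equity outcomes have no reference group, so they show coverage among minority and low-SES families but not whether the screening gap changes

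*Protocol article*

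**What the plan says.** All references are to the protocol article.

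- **Hypothesis (Specific aims, Aim 2, H2.1(b)).** TIER is expected to give "higher rates of screening for ethnic minority and socioeconomically diverse families (health equity").
- **Outcomes (Data analysis, Aim 2, H2.1).** Penetration is "families screened/families eligible, families provided feedback/families screened", pooled over all families. Health equity is "ethnic minority families screened/ethnic minority families eligible, low SES families screened/low SES families eligible".
- **Test (same paragraph).** "ANOVA will compare the effectiveness of the two implementation strategies on penetration and health equity", with an adjustment for clustering. No term for strategy by family group is given.
- **Group comparisons (H2.3c).** The additional analyses compare English- and Spanish-speaking families and "different ethnicity, race, and SES and insurance status on the outcome variables for H2.3c". Those outcomes are services and costs, not screening rates.
- **Data (Measurement/outcomes).** Sites report monthly "demographic data on all eligible and all screened (race, ethnicity, zip code, insurance").
- **Purpose.** The contributions statement beside the trial registration presents the study as testing whether implemented screening lowers health disparities. The Discussion returns to disparities and inequities.

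**The concern.** A disparity is a comparison between groups. Each H2.1(b) outcome sees one side of it: the minority rate without the non-minority rate, or the low-SES rate without the higher-SES rate. A gain shared equally by all families (H2.1(a)) also raises both H2.1(b) rates, so a favourable result is compatible with an unchanged or wider gap.

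What is at stake is the wording of the conclusion. The Aim 3 Toolkit is expected to carry evidence on how screening affects health disparities and is to be disseminated widely. A higher minority or low-SES rate under TIER could be carried into it as an equity gain although the gap was never estimated.

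**Working it through.** **1. What the outcome can distinguish.** The article gives no expected screening rates, so the following are assumptions chosen only to show the arithmetic. Let M be the minority rate and R the rate in other families.

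- Planned contrast = M(TIER) − M(training)
- Gap in a strategy = R − M; ratio in a strategy = R / M

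Take M = 60% under training and 70% under TIER, and R = 70% under training.

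| R under TIER | Planned contrast | Gap, training to TIER | Ratio, training to TIER |
|---|---|---|---|
| 75% | 70 − 60 = +10 | 10 to 5 | 70/60 = 1.17 to 75/70 = 1.07 |
| 80% | +10 | 10 to 10 | 1.17 to 80/70 = 1.14 |
| 85% | +10 | 10 to 15 | 1.17 to 85/70 = 1.21 |

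The planned outcome is +10 points in every row. The last row widens on both scales, so the possibility of widening does not depend on the scale chosen. The middle row shows why both scales are needed: the difference is unchanged while the ratio falls slightly.

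**2. Whether another planned analysis fills the hole.** The pooled penetration outcome mixes the groups. The H2.3c comparisons do not cover screening. The reference-group rate can be derived from the collected counts, but the article names neither it nor the gap as an outcome.

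**3. How precise a gap contrast would be.** The article states no power for the equity outcomes, so its overall figures serve as the starting point.

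- Total: 6 × (60 + 92 + 339) = 2946, or 1473 per strategy, which agrees with "a total of 2946, with 1473 families allocated to each strategy".
- Effective size: the article says "With an anticipated Interclass Correlation Coefficient (ICC) [65] of .005, the effective sample size is 950 per arm". With mean site size 1473/9 = 163.7, the design effect is 1 + 162.7 × 0.005 = 1.813, and 1473/1.813 = 812. Summing the three size strata separately gives 707. The stated 950 would need a mean site size of about 111. I therefore use 707 to 950; the point does not depend on which is right.
- Assumed minority share: 20% to 50%. Test: one-sided alpha 0.05, as in the article.
- Planned contrast, 60% versus 70%: power about 0.55 (707, 20%) to 0.95 (950, 50%).
- Gap contrast when a 10-point gap closes fully (minority 60% to 70%, others 70% in both strategies): SE = √[(0.24 + 0.21)/n_M + (0.21 + 0.21)/n_R]. With 950 and a 20% share, n_M = 190 and n_R = 760, so SE = 0.0540; 0.10/0.0540 − 1.645 = 0.205, and power is 0.58. Over the whole range it is about 0.48 to 0.76.

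Applying the overall design effect to each subgroup is crude. With subgroup-specific design effects, a 20% share gives power 0.77 for the planned contrast and 0.66 for the gap; a 40% share gives 0.93 and 0.78. A site effect shared by both groups would partly cancel in the gap, which would help it. On the other side, the normal approximation ignores that there are only 9 sites per strategy. In every case calculated, the gap contrast has the lower power.

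**The case against.** The case on the other side is substantial, and much of it stands.

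- **The analysis matches the hypothesis.** H2.1(b) predicts higher rates in these families, and that is what is tested. A reader might infer that the article contradicts itself here; it does not. The weakness lies in what the health equity label can bear.
- **Coverage in these groups is worth measuring.** The aim is to screen every newly diagnosed family, so coverage among disadvantaged families matters in itself. This is why the two rates should stay.
- **H2.1(b) is not a mere repeat of H2.1(a).** A reader might infer that a positive H2.1(b) follows almost automatically once overall penetration rises. The article does not support that. If the gain fell mainly on other families, H2.1(a) could succeed and H2.1(b) fail, and power of 0.55 to 0.95 for a true 10-point gain is not automatic.
- **No false claim is pre-written.** A reader might infer that the trial will declare reduced disparities whatever the gap does. The article states no decision rule for that, and the gap can be computed from the collected data. The supportable statement is that it could be so reported.
- **Scale matters.** If rates of 60% (other) and 45% (minority) under training become 80% and 60% under TIER, the gap grows from 15 to 20 points but the ratio is 1.33 in both. No single scale should decide.
- **A gap-only rule misleads too.** If 60% and 45% under training become 50% and 45% under TIER, the gap falls from 15 to 5 points although no minority family gained. So the gap should not replace the planned outcome.

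The objection that disparity reduction is addressed through H2.3c does not remove the point. Those comparisons concern services and costs, whereas H2.1(b) attaches the health equity label to screening.

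**Conclusion.** The point holds in a limited form. As fixed in the article, the H2.1(b) outcomes answer whether TIER raises screening coverage among minority and low-SES families. They do not answer whether it narrows the screening disparity, and no other listed analysis does. In the assumed example, one +10-point result fits a gap change of −5, 0 or +5 points.

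That follows from the definition of the outcomes and needs no assumption about the true rates. The size of any misreading does depend on those rates, which the article does not give. If other families were already close to 100%, a general rise would tend to narrow the gap, but the article states no such condition. The power figures rest on assumed rates, assumed minority shares and the article's ICC of 0.005. They serve only to show that the gap contrast is the harder one to establish.

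**What to change.** 1. Keep the within-minority and within-low-SES screened/eligible rates as the H2.1(b) outcomes, with their planned comparison between strategies.
2. Add the screened/eligible rates for non-minority and for higher-SES families, using the same classification as for the existing outcomes.
3. Estimate the strategy-by-group contrast for each pair, with the H2.1 cluster adjustment. Report it with confidence intervals on both the difference and the ratio scale, and say so if the two scales disagree.
4. State in advance that TIER will be described as reducing a screening disparity only if the minority or low-SES rate is higher under TIER and the corresponding gap is also smaller. Otherwise report the H2.1(b) result as higher coverage in these groups.

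Cost: no new data, sites or visits, since the demographics are already reported monthly for all eligible and all screened families. It takes a few lines of analysis text and some further estimates. The downside is precision: the gap contrast is less precise than the within-group contrast and may be underpowered. It should therefore be read through its interval, and a wide interval should not be taken as evidence that the gap is unchanged.
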